### Ethical considerations

Since blended treatment for AUD has already been implemented in other countries, the ethical problems are scarce. Furthermore, although BLEND-A will be offered to all patients at the participating institutions, we expect that the intervention will only be implemented in 25–40% of the treatment pathways, and, thus BLEND-A will not be the only choice offered to the patients, but rather another option for treatment delivery.

The BLEND-A study has been approved by The Regional Committees on Health Research Ethics for Southern Denmark (S-201901166G). The ethics approval covers all sites involved in the study. All participants will provide written informed consent before taking part in the study.

## Discussion

The main purpose of the BLEND-A study is to examine compliance with and the effectiveness (including cost-effectiveness) of an evidence-based blended treatment program to be used in Danish alcohol treatment institutions. Specifically, BLEND-A will implement the translated and adapted treatment protocol, developed in the BLEND-A pilot study. Technically, the BLEND-A study will employ a secure internet-based treatment platform and provide access to the blended treatment program through the Danish e-Health Portal: Sundhed.dk, which allows access for citizens and health professionals. This approach will enable wide dissemination since all public health care providers are already able to connect to the portal. The combination of a national portal and a scalable and proven software solution will enable the project to take up new partners as they join the program at low cost. The cost will be kept low at the local level as IT investments are limited to training in the software and treatment workflows in the blended treatment approach.

Most of the online psychological treatments developed to target problematic alcohol use have so far been brief, low-intensity, automated programs delivered without guidance from a therapist [14, 18, 68, 69]. The problem with unguided internet-based programs is that uptake and compliance is low and translation of therapy content into daily life is difficult [70, 71]. Further, even with therapist guided treatment, compliance and treatment adherence may be lower than for face-to-face treatment [72]. While unguided interventions may be optimal for cases not fulfilling diagnostic criteria for AUD or mild AUD cases, the blended approach could be more feasible and easier to implement among patients with moderate and even severe AUD, since it still includes face-to-face treatment [7, 41–43].

When implementing Internet interventions, reluctance among patients, clinicians, and other stakeholders represent an important barrier [43, 73]; however, blended treatment seems to reduce this barrier to a considerable extent. In a stakeholder survey conducted in eight European countries involving 175 mental health organizations, results revealed greater acceptability of blended treatment compared to stand­alone internet treatments: for mild mental disorders, 47% would recommend internet-based treatment only and 70% blended treatment, but for moderate mental disorders the corresponding figures were 15.7 and 57.2%, representing a marked difference. The same discrepancy was found for severe mental disorders, with 1.9% recommending internet-based treatment and 27% blended treatments [43]. Thus, stakeholders seem much more inclined to implement blended treatment for moderate and even more severe mental disorders than they are to implement unguided and guided standalone interventions.

These findings are in line with the BLEND-A pilot study involving therapists and patients from three treatment institutions. A clear advantage of blended treatment was that the therapist and the patient could decide together whether to continue with blended treatment or proceed with TAU. Further, the therapist could assess and refer the most severe and complex AUD patients to detoxification and inpatient treatments. The therapists participating in the BLEND-A pilot study found that the blended-care approach could easily be integrated in outpatient community-based treatment for AUD. They did not consider giving written feedback on the patients’ internet-based homework as being difficult and they perceived that they had more time to reflect and focus than when giving feedback in a direct conversation. The patients participating in the pilot study expressed that they liked the mixture of face-to-face therapy and internet-based homework. They found it helpful that blended care involved homework assignments, including reading and writing tasks, and that it was possible to repeat tasks if they felt that they needed a brush-up. Finally, the pilot study indicated that a new group of patients may be reached by the blended care treatment offer. Several patients approached the treatment center specifically because they had learned about the possibility of receiving treatment over the internet that is still guided by professional therapists. These patients claimed that they would not have sought treatment if it had involved face-to-face treatment only. They appreciated the flexibility and the discretion that blended care offered [44].

The improved access to flexible treatment due to the online part of blended treatment may also prevent premature treatment drop-out, which is obviously an advantage. It has, however, also been suggested that face-to-face treatment can be too long [50]. If the treatment pathway and thereby the interaction with the therapist lasts too long, the patient may not experience an optimal transfer of new competences into daily life and the therapy may turn into a less structured and more private kind of conversation [74–76]. Blending face-to-face sessions with internet-based modules may not only be a way of preventing early treatment drop-out due to ease of access but also of preventing the patient from becoming dependent on the therapist due to patient empowerment [75, 76]. Additionally, blended treatment may help to prevent ‘therapist drift’ since the internet modules and exercises not only provide a clear working structure for the patient but also for the therapist [77]; the therapist is nudged to incorporate the full therapy protocol in the sessions, thus improving compliance with the therapy protocol on the therapist’s side [78].

Blended treatment is expected to improve compliance with treatment and prevent early drop-out. Furthermore, the overall effect of treatment for AUD might increase since more patients finalize treatment. Underserved people suffering from AUD will thus be offered state-of-the-art, evidence-based, blended treatment, and the reach of existing alcohol treatment providers will be extended. By enlarging the reach of alcohol treatment services, more people can benefit from them, including those who otherwise are not able to access services due to geographical distances, study and work schedules, perceived stigma attached to seeking treatment, and other inequitable circumstances.

The BLEND-A study will be performed and implemented in operating treatment institutions; thus, it may increase the likelihood that knowledge and experience gained from performing the study will stay in the treatment institutions after study conclusion. After the study, the treatment protocol will be offered to the treatment institutions for free, and this may help bridge the gap between the need for treatment and its provision.

Implementing and evaluating BLEND-A in routine care is the first step to creating a solid basis for integrating internet-based modules in treatment for AUD, and in particular forms the basis for estimating cost-effectiveness of the intervention. Allowing for part of the treatment to be performed via the internet with face-to-face therapist support also opens the possibility for adapting the treatment to comorbid mental disorders the patient may be suffering from. It also offers the opportunity for continuing treatment during hospitalization and during aftercare.

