**Methods:**

The study design is a pragmatic, stepped-wedge cluster randomized controlled trial. The included outpatient institutions (planned number of patients: *n* = 1800) will be randomized in clusters to implement either blended AUD treatment or face-to-face treatment only, i.e. treatment as usual (TAU). Both treatment approaches consist of motivational interviewing and cognitive behavioral therapy. Data on sociodemographics, treatment (e.g. intensity, duration), type of treatment conclusion (compliance vs. dropout), alcohol consumption, addiction severity, consequences of drinking, and quality of life, will be collected at treatment entry, at treatment conclusion, and 6 months after treatment conclusion. The primary outcome is compliance at treatment conclusion, and the secondary outcomes include alcohol consumption and quality of life at six-months follow-up. Data will be analyzed with an Intention-to-treat approach by means of generalized linear mixed models with a random effect for cluster and fixed effect for each step. Also, analyses evaluating cost-effectiveness will be conducted.

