**Fig. 1 Fig1:**
[figure not shown]
Enrollment of groups of participating institutions (clusters) to the BLEND-A intervantion

First-movers will implement BLEND-A first, and second-movers will implement BLEND-A 3 months later. Third-movers and fourth-movers will implement BLEND-A after another 3 and 6 months. Hence, the patients being treated at an institution before implementation will serve as control groups until the institution implements BLEND-A.

The randomization of the institutions into the four waves of movers occurred by 1) attributing the participating institutions a random number, and 2) elaborating six different models for implementing the institutions (numbers) into the different waves of the study. The randomization procedure was designed by the research group. The models were placed in separate envelopes and then an independent staff member (a statistician not part of the research group) selected one, which was subsequently applied to designate the institutions into first-, second-, third- or fourth movers.

All individuals seeking treatment for AUD at the participating treatment institutions during the study period will be invited to participate as a routine part of the intake procedure at the institutions.

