### Data collection

All patients from each of the participating treatment institutions will be followed up in the National Register of Alcohol Treatment (NAB). In accordance with Danish Law, this register contains data on all patients receiving publicly funded treatment for AUD. The register provides data on sociodemographic characteristics, compliance, and alcohol related variables (see Table 1).

**Table 1 Tab1:** Data collected during the BLEND-A study

Domain	Measure/source	Content	Reference	Time-point
Descriptive variables				
Sociodemographics and treatment data	National Alcohol Treatment Register (NAB)	Gender, age, education, etc. and treatment duration and intensity as well as prior treatment.	[51, 52]	Treatment entry and treatment completion
Primary outcomes				
Compliance	National Alcohol Treatment Register (NAB)	Treatment retention and type of treatment conclusion (i.e. dropout or completion).		Registered on continuous basis in the national register
Secondary outcomes				
Alcohol consumption	Alcohol Use Disorders Identification Test (AUDIT)	Items from the AUDIT: Quantitiy/frequency measure of alcohol consumption.	[53]	Treatment entry and 6-month follow-up post treatment
AUD severity	Alcohol Use Disorders Identification Test (AUDIT)	AUDIT asesses AUD, alcohol consumption, drinking behaviors, and alcohol-related problems	[53]	Treatment entry and 6-month follow-up post treatment
	Alcohol Dependence Scale (ADS):	ADS measure the severity of alcohol dependence symptoms.	[54, 55]	Treatment entry and 6-month follow-up post treatment
	Short Inventory of Problems-2 Revision (SIP-2R)	SIP-2R evaluates alcohol-related problems.	[56]	Treatment entry and 6-month follow-up treatment
	National Alcohol Treatment Register/ Addiction severity Index (ASI)	ASI assesses multidimesional addiction severity related to various domains: alcohol and drug use, physical and mental health, employment, legal problems and social functioning.	[51, 52]	Treatment entry and treatment conclusion
Quality of life	European Quality of life - 5 Dimensions (EQ5D)	EQ5D evaluates quality of life on five dimensions: mobility, self-care, usual activities, pain/discomfort, and anxiety/depression.	[57, 58]	Treatment entry and 6-month follow-up post treatment.
Usability of blended treatment	System Usability Scale (SUS)	SUS evaluates the usability of the web-based treatment system.	[59]	6-month follow-up post treatment.

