### Data analysis

In a stepped wedge study, the distribution of results across unexposed observation periods is compared with the distribution of results across the exposed observation periods [62]. The data in the present study will be analyzed using an Intention-to-treat approach and by a blinded statistician. In the BLEND-A study, the evaluation will be conducted over a 16-month period during which the proportion of clusters exposed to the blended treatment intervention gradually increases. Adjusting for the systematically different observation periods and for clustering in the data will be accomplished by fitting an appropriate generalized linear mixed model or using generalized estimating equations (GLMM). We may also decide to examine how the impact of implementing blended treatment develops (over time) once it is introduced into a cluster, since the intervention may need an initial period of adjustment before becoming fully embedded in the setting. Hence, the length of the period (up to the current observation) during which the cluster (treatment institution) has been exposed to the intervention may be included in the model as an effect modifier [62].

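### If offering BLEND-A changes who seeks treatment, a model with only step and cluster terms cannot separate that change from the effect on completion

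*Protocol article*

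**What the plan says.** **Who may come.** The Discussion states that "the pilot study indicated that a new group of patients may be reached by the blended care treatment offer". Of several pilot patients who came because of the online option, it adds: "These patients claimed that they would not have sought treatment if it had involved face-to-face treatment only". It later says that "the reach of existing alcohol treatment providers will be extended".

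**Who is compared.** Under Study procedure and randomization, "All individuals seeking treatment for AUD at the participating treatment institutions during the study period will be invited to participate", and "the patients being treated at an institution before implementation will serve as control groups until the institution implements BLEND-A". The comparison is between different people at the same institution, before and after its crossover.

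**What the model contains.** The Abstract names "generalized linear mixed models with a random effect for cluster and fixed effect for each step". The Data analysis section says "Adjusting for the systematically different observation periods and for clustering in the data will be accomplished by fitting" a suitable mixed model or generalized estimating equations. It adds time since exposure as an optional effect modifier. No patient-level covariate is named.

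**What is recorded at entry.** For the national register, Table 1 lists "Gender, age, education, etc. and treatment duration and intensity as well as prior treatment". It also lists the Addiction Severity Index at entry and at conclusion.

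**The concern.** The primary outcome is the proportion of enrolled patients who complete treatment. If the offer changes who enrols, that proportion can move even when BLEND-A changes no patient's chance of completing. Intention-to-treat analysis gives no protection, because the selection takes place before enrolment.

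The model terms do not help either. The step effect is common to all institutions, and the cluster effect is constant over time within an institution. Neither can absorb a change that starts at each institution's own crossover date.

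The first hypothesis is better compliance than under face-to-face treatment, and the article explains it by flexibility that prevents drop-out. A reader will take the estimate as evidence for that mechanism, although part of it may reflect different patients. A modest true effect could be of similar size to the shift. Only 25–40% of patients are expected to take up blended treatment, so if the effect works only through them, a 10-point overall gain needs 10/0.40 = 25 to 10/0.25 = 40 points among users.

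**Working it through.** **Inputs from the article**
- Completion under usual treatment: 31%. Target: 41%, a difference of 10 points (Power calculations).
- Expected uptake of blended treatment: 25–40% (Study design).
- 18 institutions in four waves; 1800 patients planned.

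**Inputs assumed, because the article gives no value**
- s, the share of newly attracted patients in intervention periods: 5–15%.
- p, the completion rate of those patients: 20–70%.

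The stated 80% power can be neither confirmed nor refuted, since the text gives no intra-cluster correlation (ICC). Nothing below depends on it.

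**Step 1: where the shift goes.** Suppose BLEND-A affects nobody's completion. In a control period, expected completion is 0.31 plus the step and cluster effects. In an exposed period it is (1 − s) × 0.31 + s × p plus the same effects. The difference, s × (p − 0.31), is present exactly when the exposure indicator is 1, so it is estimated as the intervention effect.

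**Step 2: size, in percentage points**

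| s | p = 20% | p = 31% | p = 50% | p = 60% | p = 70% |
|---|---|---|---|---|---|
| 5% | −0.55 | 0 | +0.95 | +1.45 | +1.95 |
| 10% | −1.10 | 0 | +1.90 | +2.90 | +3.90 |
| 15% | −1.65 | 0 | +2.85 | +4.35 | +5.85 |

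The extremes are 0.15 × (0.20 − 0.31) = −1.65 and 0.15 × (0.70 − 0.31) = +5.85. The effect is zero if new patients complete at the usual rate.

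**Step 3: plausibility of the shares.** If new patients come for blended treatment, s cannot exceed uptake. A share of 15% would mean that 15/40 = 37.5% to 15/25 = 60% of all blended users would otherwise not have come. The upper end of the range is therefore demanding.

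**Step 4: check by simulation.** The set-up was zero true effect, 18 institutions of 100 patients, four waves, ICC 0.02 (assumed) and 1000 runs per scenario. Such patients were assumed to make up 2% of control-period intake, so the expected shift is (s − 0.02) × (p − 0.31). The model was linear, with fixed step effects and a random cluster effect.
- No shift: estimate −0.2 points, false-positive rate 5.1%.
- s = 10%, p = 50%: +1.6 points (expected 0.08 × 0.19 = +1.5), 6%.
- s = 20%, p = 60%: +5.3 points (expected 0.18 × 0.29 = +5.2), 31%.
- s = 20%, p = 20%: −1.9 points (expected 0.18 × −0.11 = −2.0), 8%.

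The 20% shares lie above the range in Step 2 and serve only to show the mechanism. With a term for true patient type, these three shift scenarios gave estimates within 0.2 points of zero and false-positive rates of 4.5–5.1%. No instrument in Table 1 records that type, so this is the best case for adjustment and not what measured covariates would achieve.

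**The case against.** **The article does not rule out covariates.** It names step and cluster and leaves the exact model open, and an analysis plan that is not shown may add entry covariates. That is fair, and the article should not be read as forbidding adjustment. What remains is that the same document predicts a change in attendance and names a model that cannot separate it from the intervention effect.

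**The change in attendance may be part of the effect.** The Study design section randomises institutions to a changed offer, and the power section aims at overall completion at the institution. For that question the unadjusted estimate is the right one. This stands: a reader might conclude that the unadjusted analysis is simply wrong, and the document does not support that. The first hypothesis can also be read as a claim about comparable patients, so both estimates are needed.

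**The evidence for a shift is thin.** A reader might infer that the pilot proves the shift, or that it will inflate the result. The article says only that a new group may be reached, on the word of several patients in a pilot of 22 treatment pathways. It gives no completion rate for them, so the bias could be negative or zero.

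**Staff selection is limited.** The primary outcome comes from a register covering all publicly funded patients, which leaves little room for selective recruitment by staff. This also stands; the remaining route is patients' own decision to seek treatment.

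**Adjustment may miss the relevant traits.** Age, education or severity do not measure a wish for flexibility and discretion. That is correct, and it is why intake and entry characteristics should be tabulated as well.

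**Conclusion.** The point holds as a limitation of the stated model. Any change in case-mix that begins at crossover cannot be told apart from an intervention effect on completion. With assumed shares of 5–15% and assumed completion of 20–70% among new patients, the bias for a claim about comparable patients is about −1.7 to +5.9 points against a 10-point target. Both ranges are assumptions, so the document supports a risk of unknown size and direction and not a demonstrated inflation. At the smaller shares, the effect on the false-positive rate is slight. The improvement is worth making because it needs no new data.

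**What to change.** - Add pre-specified entry covariates from the register to the step-and-cluster model for completion: age, gender, education, prior treatment and Addiction Severity Index severity at entry. Leave out treatment duration and intensity, which arise after entry.
- Express the adjusted result as a standardised risk difference, so that it can be set against the 10-point target.
- Report it beside the unadjusted model, and state that the latter estimates the institution-level effect including any change in who attends.
- Tabulate intake numbers and entry characteristics before and after crossover, by institution. The register data from the year before enrolment can support this.

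**Cost:** some added wording and slightly more analysis, with no new data collection. Adjustment removes only the part of the shift that the measured covariates capture, and the report should say so.

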## Data Availability

The dataset is available on request from the authors, provided this is compliant with the national legislation and with the decisions of the ethical committee.

## Abbreviations

ADS: Alcohol dependence scale
ASI: Addiction severity Index
AUD: Alcohol use disorder
AUDIT: Alcohol use disorders identification test
CBT: Cognitive behavioral therapy
EQ5D: European quality of life - 5 dimensions
GLMM: Generalized estimating equations
ICERs: Incremental cost-effectiveness ratio
MI: Motivational interviewing
OPEN: Open patient data explorative network
QALYs: Quality-adjusted life-years
QoL: Quality of life
REDCap: Research electronic data capture
SIP-2R: Short inventory of problems-2 revision
SUS: System usability scale
TAU: Treatment as usual
